#### Patient-reported outcomes measurement information system (PROMIS)-preference (PROPr)

PROPr measures a participant’s health-related quality-of-life (HRQoL) across the following PROMIS domains: cognitive function abilities, depression, anxiety, fatigue, pain interference, pain intensity, physical function, sleep disturbance, and ability to participate in social roles and activities [65, 66]. PROPr is also capable of generating a health utility index value, from the participant’s scores for each domain, that represents the general United States population’s preference for the respondent’s current health state. PROPr has 5 levels for each domain, ranging from “no problems” to “extreme problems.” The health-utility value can range from − 0.022 to 1, where 0 represents death, 1 represents perfect health, and values below 0 represent states perceived to be worse than death.

### Statistical analysis/outcomes

*Specific Aim 1: Evaluate a Stepped Care approach for advancement along the PrEP Care Continuum (initiation, adherence, persistence) and reductions in substance use.*

The primary outcome for PrEP Care Continuum advancement is PrEP adherence and persistence. For those who initiate oral-daily PrEP, persistence is defined as a co-occurrence of ≥ 700 fmol/punch and ongoing use over a period of time (6 or 12 months) confirmed PrEP care medical visits. At each time point, those who initiate PrEP, attend a PrEP medical care visit in a given quarter, and evidence a DBS TFV-DP concentration of *≥* 700 fmol/punch are coded “PrEP adherent” and all others are coded as “non-adherent.” Participants who initiate PrEP, attend quarterly medical visits, and have a DBS TFV-DP concentration above the limit of quantification are coded “PrEP persistent”; all others are coded as “non-persistent”. For those who initiate long-acting injectable PrEP, adherence is defined as verified documentation of a Cabotegravir injection every 2 months, and persistence is defined as ongoing use over a period of time (6 or 12 months). Participants that discontinue PrEP due to elimination of their substance use and HIV sexual risk behaviors are categorized as persistent.

We quantify the primary intervention effects as the difference in proportion of participants who are adherent and persistent, comparing the Stepped Care intervention to SOC. We estimate this effect using longitudinal targeted minimum loss-based estimation (LTMLE) [67, 68]. This method appropriately accounts for the study design and the fact that only some participants are eligible for re-randomization, and accounts for predictive and prognostic time-varying participant-level covariates. Implementation of LTMLE involves estimating several sequential regressions modeling the probability of adherence and persistence as a function of time-varying covariates. In order to remove the potential for investigator bias in the analysis phase, we require that these regressions are fully defined a priori, which is challenging because model checking/re-fitting procedures cannot be employed while maintaining the study blind. Instead, we rely on the Super Learner for estimating these regressions [69]. The Super Learner is an ensemble machine learning approach that uses cross-validation to weight the contributions of several pre-specified candidate regression models. It can be used as a tool to pre-specify and fully automate the model selection process while remaining blinded to intervention assignments.

We study key secondary endpoints of PrEP initiation at 3-, 6-, 9-, and 12-months. PrEP initiation is operationalized dichotomously and is defined as confirmed acquisition of oral daily or long-acting injectable PrEP from a clinical provider. As with the primary analysis, we quantify treatment effects in terms of differences in probabilities of initiation and assess them via LTMLE and Super Learning.

Cumulative days of substance use are measured via TLFB, and urine drug screens, with the focus being the participant’s primary substance of concern. Self-reported substance-free days must be confirmed by non-reactive urine drug screen results; missing urine drug screens are treated as positive, consistent with the SUD literature [70]. We quantify treatment effects in terms of the difference in average cumulative days of substance use at 3-, 6-, 9-, and 12-month follow-up visits. The secondary substance use outcomes include the cumulative: (a) proportion of positive urine drug screens at 3-, 6-, 9-, and 12-months [71]; and (b) days of self-reported substance use at 3-, 6-, 9-, and 12 months. These analyses also leverage LTMLE and Super Learning.

The analyses of the primary PrEP and substance use endpoints involve two-sided hypothesis tests at the 0.05 level. We control for multiplicity of testing across the secondary endpoints [72]. For all primary and key secondary analyses, we report the point estimate in each intervention group, as well as estimated intervention effects, accompanied by appropriate confidence intervals. The clinical significance (as judged by the magnitude of the point estimate and width of the accompanying confidence interval) of our findings are described in addition to the statistical significance.

*Specific Aim 2: Estimate the cost of implementing and sustaining each intervention (Stepped Care with: a] A.S.K.-PrEP + CM; b] CM alone) and conduct a cost-effectiveness analysis to determine the value of each intervention relative to SOC, and to each other, from the healthcare-sector, state-policymaker, and societal perspectives.*

The economic analysis is conducted using well-established guidelines, from the healthcare-sector, state-policymaker, and societal perspectives [73, 74]. First, the resources and associated costs required to implement and sustain each intervention (*A.S.K.-PrEP* stepped to *A.S.K.-PrEP* + CM; *A.S.K.-PrEP* stepped to CM alone) are estimated using a detailed microcosting analysis. Second, we estimate the value of each intervention relative to SOC, and each other, including extrapolating the downstream savings resulting from improvements in SUD, and concomitant reductions in related risk behaviors. The resource costing method is used to value resources, including those identified for implementation/sustainment of the intervention, and those utilized by participants, by perspective [75]. Unit costs are derived from sources reflecting national “real-world” costs faced by the relevant stakeholders, and are adjusted for inflation [74].

The outcome of the cost-effectiveness analysis is the incremental cost-effectiveness ratio (ICER), which is calculated as the incremental cost of a given intervention relative to an alternative, divided by the incremental mean effectiveness of the two interventions. The primary measure of effectiveness for the economic evaluation is QALYs; the second is advancement along the PrEP Care Continuum. The QALY is a measure that combines the HRQoL associated with an individual’s health state and their time spent in that state, and is the foremost effectiveness measure in economic evaluation studies due to its comparability across interventions/disorders, and the existence of generally-accepted value thresholds [74, 76]. The PrEP Care Continuum is an important and widely accepted model/tool for assessing PrEP care outcomes at both an individual and a public-health level; thus, the additional cost required to achieve a one-step increase along the Continuum for the average trans woman or SMM with an SUD, has important clinical and policy implications. Two ICERs (one for each effectiveness measure) are calculated for each stakeholder perspective at both 6 months (intervention completion; immediate effects) and over the 12-month observation period (intervention + follow-up).

ICERs consist of predicted mean cost and effectiveness values. To help address censored data we model the person period and estimate all regressions using a multivariable generalized linear mixed model (GLMM) [74]. Separate multivariable GLMMs are estimated to predict the mean dollar value for each resource, the health utility value, and PrEP Care Continuum steps gained at each time period, by study arm. Predicted mean costs and steps gained are then be summed and tested over the relevant time periods (6 months, 12 months), and QALYs gained are estimated using the predicted health utility values and the area under the curve methodology, then tested [74]. Standard errors are estimated via nonparametric bootstrapping techniques within the multivariable framework. Methods to reduce bias from participant attrition and missingness are combined within the non-parametric bootstrap, following recommended approaches [67].

For each effectiveness measure, we determine which intervention is most cost-effective using the rules of strong and extended dominance. Finally, we estimate acceptability curves for each ICER, which illustrate the probability that an intervention is cost-effective for different value thresholds [77].

*Secondary Aim. Determine individual effects of specific substances, routes of administration, severity of SUD, social and structural determinants of health, and differing individual-level characteristics as moderators of outcomes.* As with Specific Aim 1, we utilize LTMLE to estimate subgroup-specific treatment effects based on participant-level characteristics. The magnitude of intervention effects are compared across relevant subgroups to infer moderation of intervention outcomes. We use Benjamini-Hochberg corrections to account for multiple testing and control for the false discovery rate of moderators.

*Exploratory Aim: Evaluate intervention engagement (i.e., number of A.S.K.-PrEP sessions in the initial 3-months) and intervention response (responders vs. non-responders) by chosen PrEP modality (i.e., oral daily or long-acting injectable).* We compare unadjusted response rates between, and average levels of engagement across the PrEP modalities using descriptive statistics. We also present covariate-adjusted analyses that account for participant-level differences. Because this analysis involves self-selected medication adherence, we control for potential confounders of PrEP modality and response. We use the theory of directed acyclic graphs to determine an appropriate set of confounders, and TMLE to estimate the impact of the PrEP modalities on response. We use controlled direct effects to quantify the impact of intervention engagement as a mediator of intervention response and determine whether there is a differential impact of PrEP modality on response after controlling for engagement [78]. Causal sensitivity analyses are used to examine the robustness of our findings to the assumption of no unmeasured confounding.

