**Fig. 1 Fig1:**
[figure not shown]
Schematic of ASK-PrEP Stepped Care, Randomized Controlled Trial Design

The trial will recruit 250 HIV-negative trans women and SMM with an SUD (*n* = 83 trans women; *n* = 167 SMM); participants will be randomized (3:1) to *A.S.K.-PrEP* (*n* = 187), or Standard of Care (SOC; PrEP education, information, and referrals) (*n* = 63). Participants in the *A.S.K.-PrEP* Stepped Care arm will receive 5 PrEP navigation sessions within 3 months and will be assessed at 3-months for intervention response; responders will maintain the *A.S.K.-PrEP* intervention, while non-responders will be re-randomized (1:1) to either add attention to their SUD (*A.S.K.-PrEP* + CM), or shift attention to their SUD (CM alone). The study uses repeated assessments at baseline and at 3-, 6-, 9-, and 12-months post-enrollment; all assessments will be administered to participants regardless of their participation or retention. All intervention content is tailored to trans women and SMM with an SUD. Participants may choose to initiate daily oral PrEP (TDF/FTC or TAF/FTC) or long-acting injectable Cabotegravir [10].

The specific aims of the research include the following:

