### Randomization ratio and power calculation

The 3:1 initial randomization ratio was selected as a means of increasing the likelihood that an adequate number of participants receive each of the two Stepped Care approaches. Because our second-stage randomization only occurs in non-responders, there is some uncertainty at baseline as to how many participants will ultimately be in each of the three arms. We used Monte Carlo simulations to establish under a range of scenarios that a sample size of *n* = 250 and the selected randomization ratios would ensure at least 80% power to detect a clinically meaningful difference of 20% or more in the proportion persistence/adherence under intervention vs. SOC.

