#### Contingency management (CM)

CM is a behavioral economics intervention that posits the application of contingencies to motivate individuals toward health-promoting behavior change [52, 53]. Behavioral economics incorporates direct and immediate reinforcement – the primary construct in the operant form of learning theory – whereby behaviors are learned through rewards. CM uses an operant reinforcement schedule that provides increasingly valuable rewards for consecutive urine samples that are nonreactive to the participant’s targeted SUD. As successive nonreactive urine samples are achieved and voucher points increase, so does one’s sense of self-efficacy to continue providing nonreactive urine samples.

At the 3-month follow-up assessment, non-responders (see Table 2) are stepped and re-randomized to CM, either in concert with *A.S.K.-PrEP* or alone. At the first CM session, a research assistant provides a 15-minute orientation to the CM procedures, which includes an explanation of the progressive, voucher-based reinforcement schedule. Thereafter, participants will meet with a research assistant thrice weekly to provide a urine sample. The CM protocol can be simplified into these guidelines: (1) participants receive a $2.50 voucher for the first nonreactive urine sample for their targeted SUD; (2) participants receive a voucher reflecting an incremental increase of $0.50 for each subsequent nonreactive urine sample; (3) participants receive a bonus of $7.50 for each 3 consecutive nonreactive urine samples; (4) vouchers are redeemable at any time for goods or services, selected by the participant, that support a healthy and pro-social lifestyle, such as groceries, camera equipment, clothing, bicycle; (5) participants who produce a urine sample that is reactive to their targeted SUD, or who fail to submit a urine sample, do not receive a voucher for that particular CM visit and their subsequent voucher value is reduced to the initial $2.50; and (6) a rapid reset procedure allows participants to return to their place in the escalating CM schedule after producing 3 consecutive nonreactive urine samples. Participants who complete the CM intervention without a reactive urine sample earn $495 in vouchers (see Table 3). If a participant is diagnosed with a SUD for two or more substances, they are asked, “Which drug do you use most despite negative consequences?” and that drug is targeted in the CM intervention.

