#### Randomization

Stratified block randomization with random block sizes is used to assign participants to each of the two initial study arms (stepped care vs. SOC, 3:1 ratio) and to assign non-responding participants at the 3-month visit to the two stepped care modalities (*A.S.K.-PrEP* + CM vs. CM alone, 1:1 ratio). To ensure balance with respect to certain covariates, participants are grouped into four strata: (1) SMM < 35 years and/or African American/Black; (2) SMM > 34 and non-African American/Black; (3) trans women < 35 years and/or African American/Black; (4) trans women > 34 and non-African American/Black. Blocked randomization lists are generated separately for each strata by generating a block of random size (block size = 4, 8, or 12 at baseline; block size = 2, 4, or 6 at 3 months).

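### Aim 2 predicts costs and effects by study arm, a grouping that does not deliver the two embedded strategies it sets out to value against standard of care

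*Protocol article*

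**What the plan says.** Under Statistical analysis/outcomes, Specific Aim 2, the interventions to be costed are given as "A.S.K.-PrEP* stepped to *A.S.K.-PrEP* + CM; *A.S.K.-PrEP* stepped to CM alone". Both are treatment sequences that start at baseline. The comparisons follow: "we estimate the value of each intervention relative to SOC, and each other".

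The same section then sets out the estimation. Separate multivariable generalized linear mixed models (GLMMs) predict the value of each resource, the health utility and "PrEP Care Continuum steps gained at each time period, by study arm". Standard errors come from a nonparametric bootstrap, and the stated bias reduction covers attrition and missingness. The resulting incremental cost-effectiveness ratios (ICERs) feed strong and extended dominance rules and acceptability curves.

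On design, the section on contingency management says "At the 3-month follow-up assessment, non-responders (see Table 2) are stepped and re-randomized to CM", and the text with Fig. 1 says "responders will maintain the *A.S.K.-PrEP* intervention". Non-responders are split 1:1.

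For Aim 1 the plan uses longitudinal targeted minimum loss-based estimation (LTMLE), which it says "appropriately accounts for the study design and the fact that only some participants are eligible for re-randomization". LTMLE is also named for the moderator aim, but not for Aim 2.

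**The concern.** A participant who responds at 3 months has followed both strategies up to that point and afterwards. A non-responder follows only one, decided by a 1:1 draw. The mean cost or effect of a strategy is therefore an average over all responders and over non-responders given that strategy's second step, in the proportions found in the whole Stepped Care arm. A summary by arm does not produce that average unless responders are attributed to both strategies and non-responders are weighted up, or predictions are standardised over response status.

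The Aim 2 text specifies the model, the grouping, the bootstrap and the bias adjustment, but contains no such step. At stake is the comparison of each strategy with SOC, and so the ranking that Hypothesis 2 predicts. A strategy could look better or worse value because of the mix of responders and non-responders in its group rather than because of what it does.

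**Working it through.** **Which meanings of arm the article offers**

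- The Randomization section will "assign participants to each of the two initial study arms (stepped care vs. SOC, 3:1 ratio". With this meaning, Stepped Care against SOC is protected by randomisation, but no strategy-specific ICER is produced.
- Hypothesis b under Aim 1 contrasts, within Stepped Care, arms that contain CM with arms that do not. These are realised treatment groups, and the CM groups hold non-responders only. Set against the whole SOC arm, they are a selected subgroup.
- The power section refers to "how many participants will ultimately be in each of the three arms" without listing the three. Read as SOC plus the two strategies, every responder sits in two arms, and the rule for attributing them is still needed.

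**Formulas**

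Let r be the 3-month response rate (not stated), R the responder mean and N the mean in non-responders given the strategy's second step.

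- Strategy mean: r × R + (1 − r) × N
- Non-responders only: N
- Responders pooled with half the non-responders, unweighted: u × R + (1 − u) × N, with u = r / [r + (1 − r)/2] = 2r/(1 + r)

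**Size for an outcome proportion** (assumed R = 0.70, N = 0.35)

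| r | Strategy mean | Non-responders only | Unweighted pooling |
|---|---|---|---|
| 10% | 0.385 | 0.350 (−3.5 points) | 0.414 (+2.9) |
| 25% | 0.4375 | 0.350 (−8.75) | 0.490 (+5.25) |
| 40% | 0.490 | 0.350 (−14.0) | 0.550 (+6.0) |

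At r = 25%, u = 0.25/0.625 = 0.40, so pooling gives 0.40 × 0.70 + 0.60 × 0.35 = 0.49.

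**Size for a cost** (the $495 voucher maximum in Table 3, r = 25% assumed). The maximum voucher cost per strategy participant is 0.75 × 495 = $371. Non-responders alone give $495; unweighted pooling gives 0.60 × 495 = $297.

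**Effect on the ICERs.** Illustrative cost/QALY values, none from the document: SOC 4,000/0.700; responders 5,000/0.760; non-responders on A.S.K.-PrEP + CM 8,000/0.720; non-responders on CM alone 7,000/0.705. At r = 0.5:

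| Grouping | A.S.K.-PrEP + CM vs SOC | CM alone vs SOC | Strategy vs strategy |
|---|---|---|---|
| Strategy means | 2,500/0.040 = 62,500 | 2,000/0.0325 = 61,538 | 500/0.0075 = 66,667 |
| Non-responders only | 4,000/0.020 = 200,000 | 3,000/0.005 = 600,000 | 1,000/0.015 = 66,667 |
| Unweighted pooling | 42,857 | 40,000 | 66,667 |

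With strategy means, CM alone stays on the frontier (61,538 < 66,667). With non-responders only it is extendedly dominated (600,000 > 66,667). Unweighted pooling leaves it on the frontier here, but with both ICERs against SOC too low. The flip depends on the inputs: at r = 0.3 CM alone is extendedly dominated under all three groupings (111,628, 600,000 and 68,354, each above 66,667).

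**Strategy against strategy.** Responders cancel. With dC and dE the non-responder differences in cost and effect, the increments between strategies are (1 − r)dC and (1 − r)dE, so the ratio is dC/dE for any r. Non-responders only gives dC and dE, inflated by 1/(1 − r). Unweighted pooling gives the factor 1 − u = (1 − r)/(1 + r), shrunk by 1/(1 + r). At r = 25% these factors are 1.33 and 0.80. The ratio survives; the increments, which the plan says are tested, do not.

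**The case against.** The strongest reply is that study arm is undefined in this sentence, and that the paragraph before it already defines the interventions as strategies. Read together, arm could mean strategy. Replication, weights and bootstrap clustering are the kind of detail a condensed article leaves to an analysis plan. The models are multivariable and fitted by person-period, so they could include response status and be standardised over it. Intervention costs are microcosted for each stepped strategy, so the voucher arithmetic above may not describe how that component is averaged. One reference cited for LTMLE is also cited for the Aim 2 bias methods.

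Part of this stands. A reader might infer that the economic analysis ignores the re-randomisation. The article does not say so: it does not exclude responders or state that data are unweighted. It makes no provision, which is a weaker statement. A reader might also infer that every strategy-specific ICER is biased. That is wrong, because the ratio between the two strategies is preserved under both naive groupings, as is strong dominance between them, since the increments keep their signs.

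What does not stand is that this is only missing detail. The article prescribes a grouping, and no use of arm in it yields the strategy mean without a further step. The shared reference is cited in Aim 2 for attrition and missingness, not for partial re-randomisation.

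**Conclusion.** The concern holds in a limited form. The grouping stated for Aim 2 does not match the strategies Aim 2 sets out to value. Depending on what study arm means, it gives either no strategy-specific ICER, or two ICERs against SOC that are generally biased, together with the extended-dominance ranking and acceptability curves that use them. The strategy-versus-strategy ratio is essentially unaffected; that invariance is exact for differences in means and could shift somewhat under a non-identity link with shared parameters. Its increments would be inflated by 1/(1 − r) or shrunk by 1/(1 + r).

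The sizes rest on assumed response rates and assumed outcome, cost and QALY values. What is general is the direction of the argument: bias arises whenever responders and non-responders differ in cost or effect. The point should be corrected before the economic analysis is run. It does not touch the Aim 1 analysis.

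**What to change.** In the Aim 2 text, replace the grouping by study arm with a grouping by strategy: SOC and the two embedded Stepped Care strategies. State that each responder counts in both strategies with weight 1, that re-randomised non-responders count in their own strategy with weight 2 (the inverse of the 1:1 probability), and that the bootstrap resamples participants so that a responder's replicated records stay together. Alternatively, extend the Aim 1 LTMLE to cost, utility and continuum steps.

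The cost is a change of wording, modest programming and slightly wider intervals from the weighting. No new data are needed, and data collection is expected to run to April 2027.

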#### Exploratory Aim 1:

Evaluate intervention engagement (number of *A.S.K.-PrEP* navigation sessions in the initial 3-months) and intervention response (responders vs. non-responders) by chosen PrEP modality (i.e., oral daily [TDF/FTC or TAF/FTC] or long-acting injectable cabotegravir).

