### Interventions

#### A.S.K.-PrEP intervention

*A.S.K.-PrEP* is a PrEP navigation intervention with SMS support. The navigation component is based on mechanisms of the Reasoned Action Approach [50], and the SMS support component is based on Social Support Theory [51]. The *A.S.K.-PrEP* intervention was adapted from Anti-Retroviral Treatment and Access to Services (ARTAS), the 5-session Centers for Disease Control and Prevention (CDC) evidence-based intervention, delivered over 3 months, for linking PWH into HIV care. Formative work was conducted to modify ARTAS to focus on linking high-risk, HIV-negative trans women and SMM into PrEP care [49]. In Session 1, the PrEP navigator uses the Needs and Barriers Assessment (NBA) to identify those pertaining to PrEP care, including substance use and behavioral health needs; adherence goal(s); and methods to achieve adherence. PrEP (TDF/FTC, TAF/FTC, Cabotegravir) and clinic options are discussed. In Sessions 2–5, PrEP navigators use the information from the NBA to help participants overcome barriers to PrEP adherence, and work with participants to address their SUD and need for additional auxiliary services.

A shorter version of the NBA (NBA-Lite) is administered at the beginning of Sessions 2–5 as a check-in and to assess progress through the PrEP Care Continuum; participant-centered treatment plans are reviewed and revised as needed. The participant-centered dialogical strategies are premised on Reasoned Action Approach: (1) identify barriers to PrEP, including substance use; (2) identify the participant’s readiness to address their SUD and link into other auxiliary needed services; and (3) increase the participants’ skills and self-efficacy in working with PrEP providers and other social service and treatment facilities. The PrEP navigator will link participants into SUD treatment and other ancillary behavioral health and support services, according to their unique barriers, with the ultimate goal of PrEP initiation, adherence, and persistence; services may include mental healthcare, counseling for intimate partner violence, food insecurity, housing instability, hormone therapy, among others. Discussions of PrEP adherence, reductions in substance use, substance use treatment, and other behavioral health concerns are discussed throughout the 5 sessions (see Fig. 2). All PrEP navigators are all peers, with past lived experiences directly related to the participants.

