**Step Criteria Based on PrEP:**
Has not initiated PrEP (either Truvada, Descovy or Cabotegravir)
On oral-daily PrEP but self-reports non-adherence (missed 4 or more days in a row) in past 3 months
On long-acting injectable but has not received 2nd dose within +/- 7 days of 28 days (i.e., 35 days) after 1st dose (only check this if 3-month follow-up takes place 35 days or more after 1st dose)

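### Exploratory Aim 1 makes the whole 3-month session count a mediator of the PrEP-modality effect, although some sessions precede the choice of modality, and part of response is scored by modality-specific rules

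*Protocol article*

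**What the plan says.** Exploratory Aim 1 in the protocol article is to evaluate session engagement and "intervention response (responders vs. non-responders) by chosen PrEP modality". The analysis is set out under Statistical analysis/outcomes. Engagement is the "number of A.S.K.-PrEP sessions in the initial 3-months". Unadjusted response rates and average engagement are compared by modality. TMLE then estimates the effect of modality on response, with confounders chosen from a directed acyclic graph. Finally: "We use controlled direct effects to quantify the impact of intervention engagement as a mediator of intervention response", so as to "determine whether there is a differential impact of PrEP modality on response after controlling for engagement". A sensitivity analysis covers unmeasured confounding.

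The timeline is given elsewhere. Participants in the Stepped Care arm "will receive 5 PrEP navigation sessions within 3 months and will be assessed at 3-months for intervention response". In Session 1, "PrEP (TDF/FTC, TAF/FTC, Cabotegravir) and clinic options are discussed" (A.S.K.-PrEP intervention). The same section says that navigators link participants to services "with the ultimate goal of PrEP initiation, adherence, and persistence".

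Table 2 sets the step criteria at 3 months:
- **No PrEP started:** a step criterion in itself.
- **Oral PrEP:** a self-reported run of at least four missed days in the past 3 months.
- **Injectable PrEP:** a second dose not received in its window, with the instruction "only check this if 3-month follow-up takes place 35 days or more after 1st dose".
- **Substance use, whatever the modality:** any recent self-reported use of the targeted substance, or a positive urine screen for it.

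**The concern.** A mediator has to follow its exposure. Here the exposure is the modality, and the proposed mediator is a session count that starts before the modality is chosen for anyone who enters without PrEP. Sessions that help to bring about initiation, and may steer the choice, are possible common causes of modality and response. If they are called a mediator, two things can go wrong. The total modality effect may be estimated without them and so be confounded. The change seen when they are added may then be reported as an effect carried through engagement.

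Separately, the two modality groups are not scored alike on the PrEP part of response, and recent injectable starters cannot fail it. Confounder adjustment does not remove a difference that arises from how the outcome is scored. The trial could credit one modality with better response when part of the difference comes from the rule.

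**Working it through.** The article gives no sample size, power or effect for this aim, so there is no figure to reproduce. The check is structural, with two illustrations on stated assumptions.

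**1. Time order.** The count covers months 0 to 3. Options are raised in Session 1, and initiation is one of the goals of the sessions. For a participant not on PrEP at entry, the count is therefore sessions before the choice plus sessions after it, and the first term is at least 1. The article does not split the count and does not say when modality is chosen. The inclusion criteria also admit people who previously initiated PrEP, for whom the choice may predate all sessions.

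**2. What the mediator label can produce.** Assumed simulation of 2,000,000 participants:
- one binary baseline covariate;
- 0 to 5 sessions, depending on that covariate;
- sessions raise the log-odds of choosing injectable (0.3 or 0.5 per session) and of responding (0.3 or 0.5 per session);
- modality has no effect on sessions or on response.

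| Session effect on choice / on response | Modality effect, baseline covariate only | Holding sessions fixed | Apparent mediation |
|---|---|---|---|
| 0.3 / 0.3 | +2.4 points | about 0 | 2.4 points |
| 0.5 / 0.3 | +3.8 points | about 0 | 3.9 points |
| 0.5 / 0.5 | +6.1 points | about 0 | 6.2 points |

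The truth is zero in every column. The error lies in the total effect and in the mediated part. The contrast holding sessions fixed is right in these scenarios, where all sessions precede the choice and nothing is unmeasured. The simulation does not cover a count that mixes earlier and later sessions. There, the total need not stand in for the earlier sessions, so the contrast may survive but this is not assured.

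**3. Unequal scoring of the PrEP criterion.** Suppose that first injections are uniform from day a to day 90 and that the true failure probability is q in both groups. The share of injectable starters not checked is 35/(90 − a), which is 35/90 = 39% for a = 0 and 35/60 = 58% for a = 30.

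- *Every oral user fails at the full rate q.* The gap favouring injectable is q × share. With q = 30% and a = 0, scored injectable failure is 0.611 × 30% = 18.3% against 30% for oral, a gap of 11.7 points. Over q = 20% to 60% and a = 0 to 30, the gap runs from 0.2 × 0.389 = 8 points to 0.6 × 0.583 = 35 points.
- *Oral starts are spread over the 90 days in the same way.* With constant hazard and 30% failure over 90 days, hazard × 90 = −ln(0.70) = 0.357. Mean scored oral failure is 1 − 0.30/0.357 = about 16%, against 18.3% for injectable. The gap is now about 2 points in the other direction.

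Size and sign therefore depend on start dates, which the article cannot give.

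**4. Dilution by the common criteria.** Assume that any single criterion makes a participant a non-responder, and that a share s passes the substance-use criteria independently of PrEP status. The gap in overall response is then s × the gap on PrEP. For 11.7 points, s = 20% gives 2.3, s = 50% gives 5.9 and s = 75% gives 8.8.

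**5. What the stated safeguards cover.** The graph step selects confounders of modality and response, but the text has already assigned engagement to the mediator role. The sensitivity analysis addresses unmeasured confounding. Neither addresses time order or scoring that differs by modality.

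**The case against.** The other side has a good deal right. Three stronger readings are tempting, and the documents do not support them.

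- **That the sessions largely precede the choice.** No date of choice is given. Options are raised in Session 1, so four of the five sessions could follow it. With assumed even spacing and uniform start dates, about 2.8 to 4.2 of the 5 sessions precede PrEP start, but that rests on the assumptions.
- **That the aim cannot be answered.** It asks for engagement and response by modality. Comparing engagement by modality needs neither a causal order nor the response rule, and response can be described with a caveat about scoring. Non-initiators fall outside a by-modality question by definition; that is a matter of reporting them.
- **That scoring creates a 12-point artefact.** That figure gives every oral user a full 90 days at risk while spreading the injectable starts. With both spread alike, the gap is small and reversed. Moreover, an injectable user still inside the window has not failed under the rule.

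It can also be said that the graph could place earlier sessions among the confounders, and that an analysis plan not shown may settle the detail. This stands only in part. The article does not merely leave the role of engagement open; it states it as mediator for an undivided count. It also plans the response comparison by modality without a step for the differing rules.

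**Conclusion.** The point holds in limited form. For participants not already on PrEP, at least Session 1 precedes the choice of modality, so the undivided count cannot be read simply as a mediator. The mediation reading, and a total modality effect that omits earlier sessions, can be biased, by about 2 to 6 points in the scenarios assumed. The engagement-adjusted contrast is not invalidated by the ordering alone, provided that the earlier sessions are in effect held fixed and confounding is otherwise controlled.

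Part of any modality difference in response may reflect scoring. Its size and direction cannot be fixed from the article: about 12 points favouring injectable to about 2 points favouring oral at 30% true failure, and less in overall response because the substance-use criteria are shared.

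The primary and secondary analyses are not touched. The change is still worth making before analysis, since it prevents a false mediation finding. The article expects data collection to finish in April 2027.

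**What to change.** In the Exploratory Aim text under Statistical analysis/outcomes:

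1. Split the session count at each participant's PrEP start, or at modality choice if recorded. Enter earlier sessions as confounders, and analyse only later sessions as a possible mediator.
2. Report the PrEP and substance-use components of response separately by modality.
3. Identify injectable starters not yet assessable and show results with and without them, or restrict both modalities to the same minimum time since start.
4. Report non-initiators as their own group.

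Do not substitute adherence coded at 6 months as a common outcome. The article also defines it by modality (drug level plus care visit for oral, documented injections for injectable), and by then the non-responders have been re-randomized. The step criteria themselves need no change for this point.

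The cost is analysis wording, provided that session dates and PrEP start dates are held; the article does not say so for session dates, and this should be confirmed. There will be fewer sessions after PrEP start per participant, so the mediation estimate will be less precise. The descriptive comparison of engagement by modality is unaffected.
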